#### 7. Satisfaction with the intervention

Satisfaction with the intervention will be assessed in the intervention arm only. For this purpose a satisfaction questionnaire is developed consisting of questions about: (1) the perceived efficacy of and satisfaction with the intervention program, (2) need for changes to the program, (3) the willingness to recommend the program to other patients undergoing high dose chemotherapy and SCT. A short evaluation questionnaire will also be administered to health care providers.

### 9.3 Other measurements

#### 1. Clinical data, disease status and treatment

Clinical data, including date of diagnosis, stage and subtype of disease, and treatment history will be obtained from the medical records. During the follow up-period data on disease status (response to treatment, progression or relapse) and data on any additional treatment will be retrieved from the medical records. At T0, T1 and T2, a complete blood count (haemoglobin, platelets, WBC) will be performed in patients for whom no recent (< 3 weeks) blood values are available.

#### 2. Sociodemographic and clinical data

Sociodemographic data such as age, education, marital status, living situation, medication use (including alternative medications) and life style variables (e.g. smoking) will be obtained at baseline using a questionnaire.

#### 3. Moderating variables

A series of questions will be used to assess a number of potential moderating variables: (1) pre-illness lifestyle, (2) current attitudes towards and beliefs about exercise in general, (3) exercising after stem cell transplantation in particular, (4) potential predictors of compliance with the exercise program. These questions are adapted from measures developed by Courneya and colleagues for use in evaluating exercise in cancer survivors, and are based on health behaviour theories, in particular the Theory of Planned Behaviour [51]. They will be asked at baseline only.

#### 4. Costs from a societal perspective

Costs will be measured from a societal perspective. The following are considered in this study:

- Health care costs: the costs of oncological care, general practice care and physiotherapy; additional visits to other health care providers, prescriptions of medication, professional home care and hospitalization.
- Patient and family costs: out-of-pocket expenses (e.g. travel expenses), costs for sports and sports equipment, and costs of paid and unpaid help.

- Costs due to loss of production (absenteeism for patients with paid jobs and hours of inactivity for patients without a paid job).

These data will be collected through retrospective cost questionnaires administered on a monthly basis during the period between T=0 and T=1, and once every 3 months in the period between T=1 and T=2. Health care utilization will be valued using Dutch cost prices [52].

#### 5. Adverse Events

The grading of toxicity and adverse events will be done using the most recent version of the NCI Common Terminology Criteria for Adverse Events, CTCAE version 4. A complete document may be downloaded from the following site:

<http://ctep.cancer.gov/reporting/ctc.html>

### 9.4 Monitoring of compliance and attrition

Compliance with the exercise program in the intervention arm will be assessed by self-report and by objective measures (e.g., attendance at and duration of the exercise sessions, exercise logs, target intensity). Reasons for noncompliance/nonattendance will be recorded.

Subjects can withdraw from the study at any time for any reason if they wish to do so without any consequences. When applicable, patients will be approached to ask for their reasons. The investigator can decide to withdraw a subject from the study for urgent medical reasons. Individual subjects will not be replaced after withdrawal. The principle of intention-to-treat will be applied in this study. Subjects who have withdrawn from treatment will be asked to participate in the follow-up measurements.

## **10. Safety reporting**

### **10.1 Adverse event (AE)**

An adverse event (AE) is any untoward medical occurrence in a patient or clinical study subject during protocol treatment. An AE does not necessarily have a causal relationship with the treatment. An AE can therefore be any unfavourable and unintended sign (including an abnormal laboratory finding), symptom, or disease temporally associated with the treatment whether or not related to the treatment.

### **10.2 Serious adverse event (SAE)**

A serious adverse event is defined as any untoward medical occurrence that at any dose results in:

- death.
- a life-threatening event (i.e. the patient was at immediate risk of death at the time the reaction was observed).
- hospitalization or prolongation of hospitalization.
- significant / persistent disability.
- any other medically important condition (i.e. important adverse reactions that are not immediately life threatening or do not result in death or hospitalization but may jeopardize the patient or may require intervention to prevent one of the other outcomes listed above).

Note that ANY death, whether due to side effects of the treatment or due to progressive disease or due to other causes is considered as a serious adverse event.

#### 10.2.1 Unexpected SAE

Unexpected serious adverse events are those SAE's of which the nature or severity is not consistent with information in the relevant source documents.

### **10.2 Protocol treatment period**

The protocol treatment period is defined as the period from the baseline measurements (T0) until 30 days of the end of treatment (T1 or until the start of another systemic anti-cancer treatment off protocol, if earlier.

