### **10.3 Reporting of serious adverse events**

During protocol treatment all deaths, all SAE's that are life threatening and any unexpected SAE must be reported to the study coordinators by fax within 24 hours of the initial observation of the event, except hospitalizations for:

- a standard procedure for protocol therapy administration. Hospitalization or prolonged hospitalization for a complication of therapy administration will be reported as a serious adverse event.
- the administration of blood or platelet transfusion. Hospitalization or prolonged hospitalization for a complication of such transfusion remains a reportable serious adverse event.
- prolonged hospitalization for technical, practical, or social reasons, in absence of an adverse event.
- a procedure that is planned (i.e., planned prior to starting of treatment on study; must be documented in the source document and the CRF).

All details should be documented on the Serious Adverse Event and Death Report. In circumstances where it is not possible to submit a complete report an initial report may be made giving only the

mandatory information. Initial reports must be followed-up by a complete report within a further 14 calendar days. All SAE Reports must be dated and signed by the responsible clinical investigator or one of his/her authorized staff members. At any time after the protocol treatment period, unexpected serious adverse events that are considered to be at least suspected to be related to protocol treatment must also be reported to the study coordinators using the same procedure, within 48 hours after the SAE or death was known to the investigator. The investigator will decide whether the serious adverse event is related to the treatment (i.e. unrelated, unlikely, possible, probable, definitely and not assessable) and the decision will be recorded on the Serious Adverse Event and Death Report. The assessment of causality is made by the investigator using the following relationship description:

**UNRELATED:** There is no evidence of any causal relationship

**UNLIKELY:** There is little evidence to suggest there is a causal relationship (e.g. the event did not occur within a reasonable time after administration of the trial medication). There is another reasonable explanation for the event (e.g. the patient's clinical condition, other concomitant treatments).

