**POSSIBLE:** There is some evidence to suggest a causal relationship (e.g. because the event occurs within a reasonable time after the assessments). However, the influence of other factors may have contributed to the event (e.g. the patient's clinical condition, other concomitant treatments).

**PROBABLE:** There is evidence to suggest a causal relationship and the influence of other factors is unlikely.

**DEFINITELY:** There is clear evidence to suggest a causal relationship and other possible contributing factors can be ruled out.

**NOT ASSESSABLE:** There is insufficient or incomplete evidence to make a clinical judgement of the causal relationship.

The study coordinators will forward all reports within one working day of receipt to the central data manager. The report of an SAE will be the signal for the data manager to ask the investigator to complete and send as soon as possible all relevant information for the involved patient with details of treatment and outcome. It is of utmost importance that all SAE's (including all deaths due to any cause) are reported in a timely fashion.

Patients without a report of an SAE are implicitly considered alive without SAE. This information will be used in monitoring the incidence of SAE's, the estimation of overall survival and safety monitoring. The study coordinator has responsibility for reporting such events to the Ethics Committee, which approved the study within the required timelines. The study coordinator will report to all applicable Health Authorities within required timelines.

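### As worded, section 10.2 can end full SAE reporting when another systemic cancer therapy starts, even though the patient may still be training; the start window in 7.2 also does not fit late second-route entrants.

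*Protocol*

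**What the plan says.** All references are to the Protocol, in which two sections carry the number 10.2.

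- **Length of the period.** Section 10.2 (Protocol treatment period) starts it at T0 and ends it "until 30 days of the end of treatment (T1 or until the start of another systemic anti-cancer treatment off protocol, if earlier".
- **Reporting inside the period.** Section 10.3 requires that all deaths, all life-threatening SAEs and "any unexpected SAE must be reported to the study coordinators by fax within 24 hours of the initial observation of the event". Relatedness plays no part.
- **Reporting afterwards.** What remains is "unexpected serious adverse events that are considered to be at least suspected to be related to protocol treatment", with a 48-hour limit.
- **General statements in 10.3.** It stresses that all SAEs ("including all deaths due to any cause) are reported in a timely fashion") matter. It also sets a default: "Patients without a report of an SAE are implicitly considered alive without SAE". That default feeds SAE incidence, overall survival and safety monitoring.
- **Definitions.** Section 10.2 (Serious adverse event) makes "ANY death, whether due to side effects of the treatment or due to progressive disease or due to other causes" an SAE. Section 10.1 defines an adverse event as "any untoward medical occurrence in a patient or clinical study subject during protocol treatment".
- **Stopping training.** Section 8.3 lists early relapse, injury or disease, poor compliance, death and completion. Starting other cancer therapy is not listed.
- **Other therapy is foreseen.** Section 9.3 says that during follow-up "data on any additional treatment will be retrieved from the medical records", and Table 2 schedules this at T0, T1 and T2.
- **Entry and start.** Section 7.3 has two routes: 6 to 12 weeks after SCT, or less than 8 months after SCT with radiotherapy or consolidation finished 2 to 6 weeks earlier. Section 7.2 gives one start window for the program, 6-14 weeks after SCT.

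**The concern.** A safety period should cover the time a patient is exposed to the trial intervention. Here its end depends on something else, the start of another cancer therapy, and nothing in section 8.3 makes training end at the same moment. A patient could be doing supervised high-intensity training with the full reporting period already closed.

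The events at stake are those that the narrower rule omits: deaths and life-threatening events judged expected or unrelated, and unexpected SAEs judged unrelated. In an open exercise program, the local judgement of relatedness is the step one would least want to rely on alone. The default in 10.3 adds to this, because silence is read as survival without an SAE and not as missing information.

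The 7.2 mismatch is a separate and smaller matter. The protocol states one start window for everyone but admits some patients who cannot meet it.

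**Working it through.** **Step 1. Reporting rules side by side (section 10.3).**

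| Event | Within the period | After the period |
|---|---|---|
| Death, judged unrelated or expected | Yes, 24 hours | Not required |
| Life-threatening SAE, judged unrelated or expected | Yes, 24 hours | Not required |
| Unexpected SAE, judged unrelated | Yes, 24 hours | Not required |
| Unexpected SAE, suspected related | Yes, 24 hours | Yes, 48 hours |

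**Step 2. Can a patient be training after the period has closed?**

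- Entry: the 6-12 week route in 7.3 sets no condition on consolidation still to come, and no exclusion criterion covers it.
- The population: the second route shows that consolidation after SCT does occur.
- Stopping: a patient without relapse who begins such therapy meets none of the reasons in 8.3 by that fact alone.

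So the combination is allowed by the text. The documents do not say that it will occur.

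**Step 3. Readings of the clause in 10.2.**

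- *The earlier of two dates.* The period ends 30 days after T1 or at the start of other systemic therapy, whichever comes first. This is the most natural sense of the closing words. For the patient in step 2, the right-hand column of the table applies while training continues.
- *Tail only.* The other therapy shortens just the 30 days after T1. On schedule the full period is 18 × 7 + 30 = 156 days, if training starts at T0 and T1 falls at its end. At most the last 30 days are then cut, and no training session lies outside.
- *On treatment as 8.3 defines it.* The 24-hour rule speaks of protocol treatment, which 8.3 does not end for this reason. The 24-hour rule then continues. However, the defined period in 10.2 has closed, so the 48-hour rule also applies, and an unexpected, suspected-related SAE has two deadlines.

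The opening bracket in the 10.2 clause is not closed in the text available. That may come from the PDF conversion, and nothing here depends on it.

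**Step 4. How many patients?** The documents give no figure for non-relapse systemic therapy started after enrolment. The one related figure is early relapse in section 11.1: 15%, or 0.15 × 120 = 18 patients. It does not size this group, because relapse takes a patient off training under 8.3.

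**Step 5. The start window in 7.2.**

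- First route: entry at 6-12 weeks plus a lag of 0-2 weeks (assumed) gives 6-14 weeks, which reproduces the stated window.
- Second route: 8 months × 30.44 days / 7 = 34.8 weeks after SCT. The latest entry is therefore up to 34.8 − 14 = 20.8 weeks past the limit in 7.2.
- A second-route patient who starts by week 14 complies. The conflict concerns only those who enter later.

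**The case against.** The strongest reply is that the 24-hour rule is tied to protocol treatment, and section 8.3 says when that ends. A patient still training is then still covered. The same argument keeps the adverse-event definition in 10.1 alive. A second reply is that the therapy meant in 10.2 is what a patient receives after relapsing and leaving the trial treatment, so that the cut-off and the end of training coincide. A third is that the separate entry route for patients with consolidation suggests they were meant to finish it first.

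These readings are possible, but they do not settle the matter. Section 10.2 contains the only definition of the period, and it names neither relapse nor 8.3. The first reading leaves two deadlines for the same event. The intention behind the second route is not stated as a condition on the first.

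The offsets are real. Related unexpected SAEs stay reportable at any time, every death is an SAE by definition, Table 2 has adverse-event entries at T1 and T2, and disease status and further treatment come from medical records. The general appeal in 10.3 to report all SAEs also helps, but it conflicts with the narrower rule and gives no deadline of its own. Visit-based collection does not replace expedited reporting.

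It is also fair to say that full reporting during other therapy is partly a matter of preference, since many of the added events will come from that therapy.

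**Conclusion.** The point holds as a minor one. On its most natural reading, 10.2 separates the full SAE period from exposure to training for a patient without relapse who starts other systemic therapy and trains on. On the kindest reading that keeps such a patient covered throughout training on the strength of 8.3, reporting is governed by two inconsistent rules. The tail-only reading avoids both problems during training, but the text does not establish it.

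The size is unknown. The affected group is conditional, is not counted anywhere in the documents and may be small.

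A reader might infer more, without support from the documents:

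- *That a given share of the safety window or of the sessions is lost.* This would need dates at which other therapy starts, and the protocol gives none.
- *That the 15% with early relapse are affected.* They leave training under 8.3.
- *That safety reporting stops.* It narrows.
- *That the efficacy results are biased or the trial loses power.* Nothing here bears on the primary analysis or the sample size, no harm has been shown, and the reviews described in section 5.1 met no negative effects.
- *That the whole second route breaks 7.2.* Only entrants after week 14 do, and the protocol attaches no consequence to it.

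**What to change.** **Main change, section 10.2 (Protocol treatment period).** Define the full SAE period as T0 until 30 days after the end of the exercise program, and until 30 days after T1 for controls, regardless of any other anti-cancer treatment. This ties reporting to exposure and removes the double deadline. It leaves randomization, sample size and analysis untouched. The cost is one sentence, plus some additional SAE reports from patients on other therapy, many of them unrelated to exercise.

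**Secondary consistency correction, section 7.2.** State that the start at 6-14 weeks after SCT applies to patients entering by the first route in 7.3. This costs one sentence and changes nothing in the conduct of the trial.

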### **10.3 Reporting of serious adverse events**

During protocol treatment all deaths, all SAE's that are life threatening and any unexpected SAE must be reported to the study coordinators by fax within 24 hours of the initial observation of the event, except hospitalizations for:

- a standard procedure for protocol therapy administration. Hospitalization or prolonged hospitalization for a complication of therapy administration will be reported as a serious adverse event.
- the administration of blood or platelet transfusion. Hospitalization or prolonged hospitalization for a complication of such transfusion remains a reportable serious adverse event.
- prolonged hospitalization for technical, practical, or social reasons, in absence of an adverse event.
- a procedure that is planned (i.e., planned prior to starting of treatment on study; must be documented in the source document and the CRF).

All details should be documented on the Serious Adverse Event and Death Report. In circumstances where it is not possible to submit a complete report an initial report may be made giving only the

mandatory information. Initial reports must be followed-up by a complete report within a further 14 calendar days. All SAE Reports must be dated and signed by the responsible clinical investigator or one of his/her authorized staff members. At any time after the protocol treatment period, unexpected serious adverse events that are considered to be at least suspected to be related to protocol treatment must also be reported to the study coordinators using the same procedure, within 48 hours after the SAE or death was known to the investigator. The investigator will decide whether the serious adverse event is related to the treatment (i.e. unrelated, unlikely, possible, probable, definitely and not assessable) and the decision will be recorded on the Serious Adverse Event and Death Report. The assessment of causality is made by the investigator using the following relationship description:

**UNRELATED:** There is no evidence of any causal relationship

**UNLIKELY:** There is little evidence to suggest there is a causal relationship (e.g. the event did not occur within a reasonable time after administration of the trial medication). There is another reasonable explanation for the event (e.g. the patient's clinical condition, other concomitant treatments).

**POSSIBLE:** There is some evidence to suggest a causal relationship (e.g. because the event occurs within a reasonable time after the assessments). However, the influence of other factors may have contributed to the event (e.g. the patient's clinical condition, other concomitant treatments).

**PROBABLE:** There is evidence to suggest a causal relationship and the influence of other factors is unlikely.

**DEFINITELY:** There is clear evidence to suggest a causal relationship and other possible contributing factors can be ruled out.

**NOT ASSESSABLE:** There is insufficient or incomplete evidence to make a clinical judgement of the causal relationship.

The study coordinators will forward all reports within one working day of receipt to the central data manager. The report of an SAE will be the signal for the data manager to ask the investigator to complete and send as soon as possible all relevant information for the involved patient with details of treatment and outcome. It is of utmost importance that all SAE's (including all deaths due to any cause) are reported in a timely fashion.

Patients without a report of an SAE are implicitly considered alive without SAE. This information will be used in monitoring the incidence of SAE's, the estimation of overall survival and safety monitoring. The study coordinator has responsibility for reporting such events to the Ethics Committee, which approved the study within the required timelines. The study coordinator will report to all applicable Health Authorities within required timelines.

## 11. Statistical considerations

### 11.1 Sample size and statistical power calculations

The sample size calculations were estimated for the primary outcomes for a two-sided  $\alpha=0.05$ , and a power of 80%. We expect a between group difference of  $7.5\pm 7$  ml/kg/min in VO2 max, of  $0.2\pm 0.1$  kg in hand grip strength and of  $3.5\pm 4$  in fatigue (MFI). We need between 25 and 42 subjects per group to detect these differences between the intervention and control group. Assuming a dropout rate of 30% (15% of the patients in our database who had undergone autologous SCT for MM< HL or NHL have an early relapse within 6 months, and are therefore expected not to complete the intervention program, and may in addition not be able to complete the study assessments. Furthermore, 15% may drop out because of other reasons) we need to enrol 60 subjects per group.

In the five participating transplant centers, yearly 180-210 autologous SCT are being performed. In 2007 170 patients received an autologous SCT for MM, HL or NHL (MM: 105 patients; NHL: 55 patients, HL: 10 patients). Taking in consideration all patients who will be ineligible for randomization (treatment related mortality SCT 4.3% = 3 patients; 10% of MM patients receiving an allogeneic SCT = 11 patients; 20% of MM patients having extensive osteolytic lesions with risk of fracture = 22 patients) we estimate that of the 170 patients transplanted yearly, 137 will be eligible, the majority of whom are expected to be interested in participating in the study (60 patients are needed on a yearly basis). This indicates that the proposed study is feasible with a projected inclusion time of 2 years.

